## Abstract

**Background:**

Randomized controlled trials showed the nonvitamin K oral anticoagulant (NOAC) edoxaban was effective and safe for stroke and systemic embolism prevention in nonvalvular atrial fibrillation (AF) and for the prevention and treatment of venous thromboembolism (VTE; including pulmonary embolism and deep vein thrombosis). Additional research is needed to evaluate the effects of edoxaban in routine clinical practice. Therefore, the Edoxaban Treatment in routine cliNical prActice (ETNA) program is being conducted to provide routine clinical care data on characteristics and outcomes in patients with AF or VTE receiving edoxaban.

**Methods:**

The Global ETNA program integrates prospectively collected data from edoxaban patients in regional ETNA noninterventional studies across Europe, Japan, and East and Southeast Asia into indication‐specific databases for AF and VTE. Targeted enrollment is >31 000 patients (AF >26 000; VTE >4500), with a follow‐up of 2 years for AF and 1 year for VTE. Data integration will be possible using consistent terminology, parameter definitions, and data collection across the regional noninterventional studies. Safety and effectiveness data will be assessed. Crude rates of outcomes including bleeding and thromboembolic events will be reported.

**Results:**

Globally, enrollment began in early 2015 and is ongoing.

**Conclusions:**

Global ETNA will generate the largest integrated prospective repository of routine clinical care data for a single NOAC in patients with AF or VTE. It will provide important information on the safety of edoxaban in routine clinical care and gather further information on its effectiveness.

## INTRODUCTION

1

Vitamin K antagonist (VKA) oral anticoagulants such as warfarin have demonstrated efficacy for stroke prevention in patients with nonvalvular atrial fibrillation (AF) and prevention and treatment of venous thromboembolism (VTE).^1^, ^2^ The non‐VKA oral anticoagulant (NOAC) edoxaban directly inhibits factor Xa to prevent thromboembolism.^3^ In the Effective aNticoaGulation with Factor Xa next GEneration in Atrial Fibrillation‐Thrombolysis in Myocardial Infarction study 48 (ENGAGE AF‐TIMI 48), once‐daily edoxaban exhibited similar efficacy for the prevention of stroke or systemic embolic events (SEE) and significantly lower rates of bleeding and death from cardiovascular causes compared with well‐managed warfarin in patients with AF.^3^ These results are broadly comparable to the other NOACs—dabigatran, rivaroxaban, and apixaban.^4^ In the Hokusai‐VTE study, once‐daily edoxaban following initial parenteral anticoagulant therapy was noninferior to warfarin for the treatment and prevention of recurrent VTE and associated with significantly fewer major and clinically relevant nonmajor bleeding events.^5^ However, there is little data on the safety and effectiveness of edoxaban in routine clinical practice settings.

Therefore, regional Edoxaban Treatment in routine cliNical prActice (ETNA) noninterventional studies were independently implemented to collect data on patient characteristics and routine clinical care outcomes in patients treated with edoxaban for stroke prevention in AF and for treatment of VTE, with the intention to integrate data through consistent a priori definitions of patient characteristics and outcomes. This design will allow for the integration of all information into Global ETNA‐AF and ETNA‐VTE databases. The set‐up will also allow for combining the AF and VTE databases.

Here, we describe the design and methodology of the Global ETNA program, the common parameters (ie, the so‐called “core data”), the observational periods, the program's differentiation from other NOAC noninterventional studies, and other technical details such as the consistency of terminology.

## METHODS

2

### Design

2.1

The Global ETNA program encompasses several multinational, prospective, observational noninterventional studies, including a European noninterventional observational study (Germany, Austria, Switzerland, Belgium, Italy, Spain, UK, Ireland, the Netherlands, and Portugal)^6^, ^7^ and similar noninterventional observational studies in Japan^8^, ^9^ and other East and Southeast Asian countries that are intended to collect regular clinical care data in edoxaban patients with AF or acute or recurrent VTE (Supplemental Table 1). Within the Global ETNA‐AF and VTE program, regional ETNA‐AF and VTE studies are registered separately. Additional countries may be added as the study progresses. Altogether, the target global enrollment for these noninterventional studies is >31 000 edoxaban‐treated patients, >26 000 of whom will have AF and > 4500 will have VTE (Table 1).

**Table 1 clc23279-tbl-0001:** Target patient enrollment and number of sites for ETNA‐AF and ETNA‐VTE per country and/or region in noninterventional studies currently open or enrolling

	ETNA‐AF		ETNA‐VTE	
	Patients	Sites	Patients	Sites
Japan	10 000	1367	≥1500	281
Europe	13 100	825	2700	282
Other East and Southeast Asian countries	3500	63	500	20
Total number of patients	26 100		4550	

Abbreviations: AF, atrial fibrillation; ETNA, Edoxaban Treatment in routine cliNical prActice; VTE, venous thromboembolism.

Power analyses for sample size justification were performed on a regional basis. Detailed sample size justification for ETNA‐AF and ETNA‐VTE Europe has been published previously.^6^, ^7^ In ETNA‐AF Japan, a total of 10 000 patients will be enrolled. Based on the interim analysis of a postmarketing surveillance of another new orally active anticoagulant, 2% of patients enrolled are expected to have severe renal impairment. The annual rate of major bleeding in patients without severe renal impairment is assumed to about 2.5% based on the results of a global AF phase 3 study^3^; the risk in patients with severe renal impairment has more than doubled. Given these assumptions, at least 8500 patients are required to detect the risk in patients with severe renal impairment during 2 years follow‐up with 80% power and two‐sided α of 5%. Assuming an expected dropout rate of 15% after 2 years follow‐up, planned enrollment is set at 10000 patients. For ETNA‐VTE Japan, a total of 1500 patients will be enrolled. According to epidemiological data, an estimated 14 674 and 7864 Japanese patients are newly diagnosed with DVT and PE, respectively, per year.^10^ Given that about 60% of patients with PE also have DVT, about 18 000 Japanese patients will develop VTE per year. Together with the expected percentage of participating institutions, VTE patients treated with edoxaban, and the feasibility of patient accrual, the planned sample size was set at 1500 or more. Assuming the incidence of major or CRNM bleeding in patients treated with edoxaban for VTE is 8.5% based on the results of a global VTE phase 3 study,^5^ a sample size of 1500 will power this study to estimate incidence at 8.5% ± 1.4% (95% CI). Assuming the incidence of recurrent VTE in the same population is 3.2%, this study is powered to estimate the incidence of recurrent VTE at 3.2% ± 0.9% (95% CI).

The ETNA protocols were approved in all participating regions and countries by the responsible ethics committees (EC) and institutional review boards (IRB) prior to initiation, except Japan, where EC/IRB approval is not required for postmarketing surveillance programs. In Japan, ETNA‐AF (UMIN000017011) and ETNA‐VTE (UMIN000016387) are conducted as part of regulatory‐required postmarketing surveillance as drug use‐results surveys; protocols were reviewed by the Pharmaceuticals and Medical Devices Agency (PMDA) prior to initiation of the noninterventional study. ETNA‐AF Europe and ETNA‐VTE Europe were designed as postauthorization safety studies as part of the risk management plan of edoxaban in order to assess the risks and benefits of the drug in European patients. The design of ETNA‐AF and VTE Europe was agreed in close collaboration with the Pharmacovigilance Risk Assessment Committee (PRAC) of EMA as a single‐arm prospective international observational study. There have been no protocol amendments following enrollment of the first patients.

Potential sites where edoxaban has been used were identified using multiple databases and selected via a stepwise process to allow representative regional distribution of types of sites and specialties. All ETNA noninterventional study participants must provide written informed consent before enrollment. Consecutive enrollment is encouraged, but not mandated; sites are not recording an exclusion list. Patients will only be included in the study after the treating physician has made the clinical decision to prescribe edoxaban for AF or an acute VTE event. Only noninterventional observations derived from routine medical care will be collected. A patient with both AF and an acute VTE event can be enrolled in only one of ETNA‐AF and ETNA‐VTE. The conduct of this project will adhere to the Declaration of Helsinki and the International Council on Harmonization Good Clinical Practice guidelines.^11^, ^12^

### Goals

2.2

The primary goal of the Global ETNA program is to integrate regional noninterventional study data into the Global databases to evaluate routine clinical usage, safety, and effectiveness of edoxaban. Individual regional ETNA noninterventional studies will obtain data on patients with AF or VTE who receive edoxaban treatment in routine clinical practice. Region‐specific findings will be reported separately. Data that are common to regional noninterventional studies will be integrated into indication‐specific global databases for analyses. This critical step allows analyses of substantially higher patient numbers than could be accomplished with individual regional studies.

### Inclusion and exclusion criteria

2.3

For ETNA‐AF, eligible patients are those treated with edoxaban for AF according to the local label. Patients enrolled in ETNA‐AF Japan were only eligible if they were receiving edoxaban for the first time to prevent ischemic stroke and systemic embolism.^9^ Patients with atrial flutter only are not eligible for enrollment in ETNA‐AF.

For ETNA‐VTE, eligible patients are those diagnosed with initial or recurrent acute VTE and treated with edoxaban according to the local label. Patients enrolled in ETNA‐VTE Europe were only eligible if the diagnosis of initial or recurrent acute VTE occurred no more than 2 weeks prior to enrollment.^7^

Due to the noninterventional design, the only exclusion criteria are not providing written informed consent or participating in a simultaneous interventional study.

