Initiation and reasons for permanent discontinuation of edoxaban will be documented, as well as information on adherence to edoxaban treatment. Data on prior anticoagulant use, including reasons for switching anticoagulants, will be collected. The follow‐up period of the regional noninterventional studies ranges from 2 to 4 years for ETNA‐AF and from 1 to 1.5 years for ETNA‐VTE; durations of follow‐up are based on regulatory authority requirements in Japan and Europe (Figure 1). Therefore, in the Global ETNA program, the consolidated follow‐up periods are 2 years for all AF patients and 1 year for all VTE patients.

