### Documentation and data assessment

2.5

Data for the ETNA noninterventional studies will be prospectively derived from medical records and the treating physicians. For the Global ETNA‐AF program, data will be collected at baseline, 1 year, and 2 years after enrollment (Figure 1). In the Global ETNA‐VTE program, data will be collected at baseline and 3, 6, and 12 months (Figure 1). Patients who permanently discontinue edoxaban during the observation period will be followed‐up for 1 year beyond discontinuation or until the end of the trial observational period, whichever comes first.

Predefined variables and definitions will be used, and free text field documentation will be limited as much as possible. Electronic case report forms (eCRFs) will be utilized in all countries and noninterventional studies except for ETNA‐VTE Japan, where paper case report forms will be completed and transcribed via double data entry into eCRFs.

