## DISCUSSION

4

By combining and integrating all regional and country‐specific noninterventional study data at a global level, the Global ETNA program is the largest integrated prospective observational program of a single NOAC, collecting detailed information on the use, safety, and effectiveness of edoxaban from more than 31 000 patients with AF or VTE and approximately 50 000 patient‐years of exposure to edoxaban. The planned enrollment of 26 000 edoxaban patients in the Global ETNA‐AF program will exceed the combined number of patients receiving a NOAC at diagnosis included in the large prospective global AF noninterventional studies GARFIELD‐AF, GLORIA‐AF, and EORP‐AF^14^, ^15^, ^16^, ^17^, ^18^; the rivaroxaban for AF routine clinical practice observational study program XANTUS has also reported lower patient numbers.^19^ As such, Global ETNA can generate a large dataset for detailed analyses. In addition, ETNA‐AF includes all‐comers with AF treated with edoxaban, while GARFIELD‐AF, EORP‐AF, and GLORIA‐AF only focus on patients newly diagnosed with AF.^18^, ^20^, ^21^

A key strength of the ETNA program is that the regional noninterventional studies are designed specifically to meet region‐specific postmarketing requirements with mandated quality standards.

The Global ETNA program will continue to include more countries and regular snapshot analyses are planned. Similar to other large prospective global AF data sets (eg, >2 years for GARFIELD‐AF; 2‐3 years for GLORIA‐AF; 3 years for EORP‐AF; and 1 year for XANTUS), the combined follow‐up period for the Global program will be 2 years for ETNA‐AF and 1 year for ETNA‐VTE (Figure 1).^17^, ^18^, ^19^, ^21^

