The integrated design of the Global ETNA core data addresses key questions about the clinical usage of edoxaban (Tables 2 and 3). These include whether the baseline clinical characteristics and outcomes in routine clinical usage of edoxaban reflect those of the pivotal randomized controlled trials and whether potential differences of dosing in routine clinical care compared with randomized clinical trials impact safety and effectiveness. Questions regarding the existence of regional usage patterns, how they affect outcomes, and how patient characteristics change over time following the introduction of edoxaban in different regions of the world can also be addressed. Finally, the timing of clinical events relative to the start of dosing, dosing interruption, resumption of dosing, or any situation leading to dose interruption can be examined.

Data on practical considerations for the use of edoxaban will be collected. For patients with AF, these include use of edoxaban with concomitant antiplatelet agents, potential differences depending on the type of antiplatelet agents (ie, aspirin, P_2_Y_12_ inhibitors), and the effects of concomitant single or dual antiplatelet therapy. The safety and effectiveness of edoxaban in patients with chronic kidney disease, including patients on the lower extreme of renal function for which edoxaban use is allowed, will also be determined. The Global ETNA database will also enable comparisons of different treatment practices in patient subgroups by country/region; indication (AF or VTE); gender; patient age, body weight, or body mass index; and others. Furthermore, Global ETNA‐AF and ‐VTE will provide routine care information on edoxaban adherence and how it changes over time, as well as the use of concomitant drugs and dosing of edoxaban in relation to the type and severity of clinical events.

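### Entry rules differ by region, so pooled early rates and regional contrasts mix patients at different times since starting edoxaban, and the article does not align time zero

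*Protocol article*

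**What the plan says.** All of this is in the Protocol article.

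- **AF entry (Inclusion and exclusion criteria).** The general rule is: "For ETNA‐AF, eligible patients are those treated with edoxaban for AF according to the local label". One region is narrower: Japanese patients "were only eligible if they were receiving edoxaban for the first time". The Discussion states that "ETNA‐AF includes all‐comers with AF treated with edoxaban". The Design section places enrolment after the decision to prescribe and gives no maximum interval.
- **VTE entry (same section).** Every region requires acute VTE. Only for Europe is it added that "the diagnosis of initial or recurrent acute VTE occurred no more than 2 weeks prior to enrollment".
- **Follow-up (Documentation and data assessment).** For AF, "data will be collected at baseline, 1 year, and 2 years after enrollment". VTE data are collected at baseline and at 3, 6 and 12 months.
- **Analysis (Goals; Common assessments and outcomes; Statistical analyses).** Regional data are merged by indication. The main outcome measures are proportions of patients with events. Crude rates are planned and Kaplan-Meier estimates are considered. No time origin is given. Common follow-up is 2 years for AF and 1 year for VTE.
- **Data and questions.** On data, the article states: "Initiation and reasons for permanent discontinuation of edoxaban will be documented". The Discussion asks how regional usage patterns affect outcomes, and says that "the timing of clinical events relative to the start of dosing" can be examined.

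**The concern.** Under the stated rules, ETNA-AF Japan is a new-user cohort, while the other AF regions may admit patients already taking edoxaban. Such prevalent users have survived and stayed on the drug up to enrolment. If the risk of bleeding or of stopping treatment is highest soon after the start, they contribute less of that early time, or none of it.

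Two results are exposed. A pooled first-year proportion could be lower than the one a patient starting edoxaban faces. And because the entry rule coincides with region, Japan could look worse than Europe or the rest of Asia with no true regional difference. The same reasoning applies to VTE recurrence and time since diagnosis, but less strongly, since all regions require an acute event.

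The Introduction justifies integration by common definitions set in advance. Entry relative to treatment start is not common to the regions, and the limitations paragraph mentions only varying treatment durations.

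**Working it through.** The article gives no figure for this effect, so there is none to reproduce. The check takes the regional shares from Table 1 and then illustrates the size under labelled assumptions.

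**Step 1: shares (Table 1 rows).**

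- AF: Japan 10 000, Europe 13 100, other Asia 3500; sum 26 600 (the printed total is 26 100). Without a stated first-use rule: (13 100 + 3500)/26 600 = 16 600/26 600 = 62.4%. Over the printed total it is 63.6%.
- VTE: Japan 1500 (a minimum), Europe 2700, other Asia 500; sum 4700 (the printed total is 4550). Without a stated 2-week limit: 2000/4700 = 42.6%.

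**Step 2: formula for AF.** Assumptions, none given in the article: the hazard is k times the later hazard h during the first 6 months on drug; new users enrol at treatment start; a share q of non-Japan patients are past 6 months at enrolment and the rest are new users; there is no true regional difference.

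- Year-1 rate, new users: h(0.5k + 0.5)
- Year-1 rate, prevalent users: h
- Prevalent share of the pool: w = 0.624q
- Relative shortfall of the pooled rate: w(k − 1)/(k + 1)
- Apparent Japan to non-Japan ratio: (0.5k + 0.5)/[(1 − q)(0.5k + 0.5) + q]

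**Step 3: results at 1 year.**

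| k | (k − 1)/(k + 1) | Shortfall, q = 0.5 (w = 0.312) | Shortfall, q = 1 (w = 0.624) | Apparent ratio, q = 0.5 | Apparent ratio, q = 1 |
|---|---|---|---|---|---|
| 1 | 0 | 0% | 0% | 1.00 | 1.00 |
| 1.5 | 0.200 | 6.2% | 12.5% | 1.11 | 1.25 |
| 2 | 0.333 | 10.4% | 20.8% | 1.20 | 1.50 |
| 3 | 0.500 | 15.6% | 31.2% | 1.33 | 2.00 |

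With k = 2 and a later rate of 2% per year, for example, new users have 3.0%. The pooled rate is 3.0 − 0.312 × 1.0 = 2.69% for q = 0.5, and 3.0 − 0.624 × 1.0 = 2.38% for q = 1. For q = 0 the shortfall is 0% whatever k is.

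**Step 4: a shorter early period.** Take the 2.5% annual major bleeding rate from the Design section as the later hazard, and confine the excess to the first 3 months. With k = 2 and q = 0.5:

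- 3-month risk, new users: 1 − exp(−0.025 × 2 × 0.25) = 1.24%
- 3-month risk, prevalent users: 1 − exp(−0.025 × 0.25) = 0.62%
- Pooled: 0.688 × 1.242 + 0.312 × 0.623 = 1.05%, which is 15.6% lower; the apparent Japan to non-Japan ratio is 1.33
- At 1 year the shortfall shrinks to 6.2% (2.887% against 3.077%)

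Over k = 1 to 3 and q = 0 to 1, the shortfall runs from 0% to 41.5% at 3 months and from 0% to 20.5% at 1 year.

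**The case against.** **Time origin is unstated.** A reader might infer that outcomes are timed from enrolment. The article does not say so: enrolment anchors the AF data-collection schedule, and the Statistical analyses section names no origin. The analysis plan, not shown, may set one. This stands. What remains is that the article itself chooses proportions over fixed follow-up windows as the main measure, and pools groups with different entry rules. A simple proportion cannot handle delayed entry.

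**Understatement is not shown.** A reader might also infer that the pooled rates are in fact too low. That needs prevalent users to be enrolled in number and an early excess hazard, and the article quantifies neither. The missing restriction elsewhere is also read from a condensed article, without the regional protocols. This stands, and is why the point is worded as a possibility. A patient enrolled a few weeks after starting still contributes some early time.

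**The VTE part is weaker.** Having no stated 2-week limit does not mean late enrolment when acute VTE is required everywhere. This stands, and no VTE bias is calculated here.

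**The aim is descriptive and much is already provided.** Crude rates in all treated patients are a legitimate description, regional findings are reported separately, and breakdown by region is allowed. That is fair for each region taken alone. It does not repair the pooled rate, whose mix of new and prevalent users depends on regional enrolment targets, or a comparison between regions whose entry rules differ.

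**Conclusion.** The point holds as a risk that the article leaves open. Entry rules differ by region, and pooled early-event and discontinuation rates may understate those of new users. Between-region contrasts may be confounded by time since treatment start.

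The groups concerned are large: 62% of the AF target and 43% of the VTE target by the Table 1 rows. The AF bias itself is unknown. It is zero if no prevalent users enrol or the hazard is constant, and about 6% to 31% of the new-user year-1 rate under the Step 2 assumptions with k from 1.5 to 3 and q from one half to one. The direction rests on risk being higher early in treatment, which is assumed.

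**What to change.** 1. Use the recorded edoxaban initiation to classify AF patients as new or prevalent users at enrolment, and report AF event and discontinuation rates separately for the two groups beside the pooled figures.
2. For between-region AF comparisons, restrict to new users or stratify by user type. For VTE, restrict to patients enrolled within 2 weeks of diagnosis, or stratify at that limit.
3. For analyses of event timing, take edoxaban start (AF) or index diagnosis (VTE) as time origin, with delayed entry at enrolment.
4. Name the difference in entry rules among the limitations.

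The work is mainly analysis-plan wording. It needs usable start dates in the core AF data and diagnosis dates in the core VTE data. The article says that initiation is documented; that a diagnosis date is held for VTE in every region should be confirmed. The main cost is fewer patients, and wider intervals, in the restricted regional comparisons.
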